## Abstract

**Introduction:**

Osteoarthritis (OA) commonly affects the ageing population, particularly the hip joint. Total hip arthroplasty (THA) is a frequent procedure that relieves pain and improves mobility, though some patients experience persistent postoperative pain. With rising numbers of THA, optimising perioperative care and pain management is crucial to address the growing clinical burden and improve patient outcomes. Positive treatment expectations have shown promise in enhancing outcomes, especially in pain management. This study implements two strategies to optimise the patient’s treatment expectations, comprising enhanced physician communication and digital social observational learning. We will examine their separate and combined effects on preoperative expectations, negative emotions, postoperative pain, inflammation and function during recovery up to 12 months postoperatively.

**Methods and analysis:**

This randomised controlled trial (RCT) investigates the impact of augmented physician communication and observational learning on treatment expectations and recovery. Participants (n=200) will be randomised into four groups: treatment as usual (TAU), augmented doctor conversation (aDOC), observational learning video (Video) and a combination of both (aDOC+Video). The aDOC group receives empathic communication and targeted information to strengthen self-efficacy. The Video group watches a model patient demonstrating successful recovery. The combined group receives both interventions. Outcomes will be assessed at multiple time points (4 days preoperatively; 1 and 4 days, 4 weeks and 3, 6 and 12 months postoperatively), including subjective pain ratings, mobility and objective physical function. The primary analysis will compare changes in pain intensity across groups. Secondary outcomes will include functional status, self-efficacy, recovery and systemic inflammatory markers. Statistical analysis involves repeated measures ANOVA and post hoc tests for between-group and within-group comparisons.

**Trial registration number:**

German Clinical Trials Register: DRKS00033212.

STRENGTHS AND LIMITATIONS OF THIS STUDYThis study uses a 2×2 factorial randomised controlled design with four intervention arms.The interventions are delivered at two timepoints: 2 days before and 1 day after surgery.The sample size was determined by a priori power analysis and accounts for dropouts.The subjective and objective outcome measures are assessed longitudinally over 12 months.Blinded outcome assessment and standardised randomisation procedures are implemented to minimise bias.

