### Blinding and randomisation

The study researcher responsible for analysing the primary outcomes will remain blinded to group allocation by working with a concealed group variable (group variable with hidden label). Since the intervention involves direct delivery by the study physician, the physician must be aware of group assignment to conduct the informed consent process using augmented communication where applicable. To minimise researcher bias, only trained study physicians deliver the augmented consultations (aDOC), while standard consultations (TAU) are provided by clinicians who are not involved in the intervention. Study staff administer the video separately after the physician’s visit, ensuring that consulting physicians remain unaware of whether a participant has received it. This design intentionally introduces a potential experimenter effect, allowing for the investigation of the impact of enhanced physician-patient interaction as part of the intervention itself (‘effects of augmented communication’). Blinding of the study researcher, who is unaware of the group allocation, is designed to minimise this risk as much as possible.

Participants will be randomly assigned to one of the four study groups using a block randomisation method to ensure balanced group sizes throughout the recruitment period. The block size will be kept constant at 20 and will not be disclosed to the physicians involved in recruitment. Allocation concealment will be achieved by using sealed, opaque and sequentially numbered envelopes. Each patient will draw one envelope on inclusion, thereby determining their group assignment by chance. This procedure ensures both randomisation integrity and transparency while minimising selection bias.

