## Objectives and Outcomes

### Primary objective (subjective pain measure)

The primary objective of this study is to reduce postoperative pain by optimising preoperative treatment expectations. Pain will be assessed using a numerical rating scale (NRS 0–10) documented in a patient diary, and the Pain and State of Health Inventory (PHI). The PHI captures both pain intensity and the subjective experience over time, enabling a multidimensional evaluation of postoperative pain.

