ASES-D, Arthritis Self-Efficacy Scale German version; Behandlungserfolg PR-OP, Perceived Treatment Success Pre-/Post-Op; CARE, Consultation and Relational Empathy Measure; CRP, C-reactive Protein; DN4 / DN2, Douleur Neuropathique 4 / Douleur Neuropathique 2; ESR, Erythrocyte Sedimentation Rate; FSS, Fatigue Severity Scale; GCPS, Graded Chronic Pain Scale; GEEE-Effekt, Göttingen Questionnaire on Experience and Evaluation of Health Care Effect scale; GEEE-Erwartung, Göttingen Questionnaire on Experience and Evaluation of Health Care Expectation scale; Harris Hip Score, Harris Hip Score; IL-6, Interleukin-6; NRS, Numeric Rating Scale; PDI, Pain Disability Index; PSS, Perceived Stress Scale; QoR-15, Quality of Recovery-15; SBI (PHI), Surgical Behavior Inventory (Pain Health Inventory); SETS, Stanford Expectations of Treatment Scale; SSAS, Somatosensory Amplification Scale; STADI Trait / State, State-Trait Anxiety-Depression Inventory; T1, 1 day postoperative; T2, day of discharge; T3, 1-month follow-up; T4, 3-month follow-up; T5, 6-month follow-up; T-4b, 4 days preoperative, after the intervention; Timepoints: T-4a, 4 days preoperative, before the intervention; Wärme u. Kompetenz, Warmth and Competence Scale.

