### Statistical analysis

Differences in clinical outcomes between and within groups will be assessed using ANOVA for the various outcome measures. Most outcomes in this study (e.g., pain intensity, functional scores and self-efficacy and inflammatory markers) are continuous and will be analysed as such. A small number of secondary outcomes, however, are categorical (e.g.,analgesic use) and will be analysed using appropriate methods, such as chi-square tests or logistic regression, depending on the data structure. Data analysis will follow the intention-to-treat principle and will be conducted by a researcher blinded to group assignments. If significant main and interaction effects are identified, post hoc analyses (e.g., Least Significant Difference (LSD)) will be performed. The statistical analyses will be carried out using IBM SPSS Statistics software version 27.0 (IBM Corp), with results presented as means and 95% confidence intervals unless stated otherwise. If required, adjustments for deviations from sphericity will be made using Greenhouse-Geisser or Huynh-Feldt corrections for the F-test df. A two-sided p-value of <0.05 will be considered the threshold for statistical significance in all analyses.

Missing data will be handled using multiple imputation, provided that the necessary assumptions are fulfilled. Participants with extensive missing data (e.g., no primary outcome data at any timepoint) will be excluded from the respective analysis. Alongside the intention-to-treat (ITT) approach, we will conduct a per-protocol sensitivity analysis, excluding participants who did not receive the full assigned intervention. This enables us to assess the robustness of results at different levels of complexity.

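### Blinded outcome assessment is listed as a strength, but the methods describe a blinded analyst and a self-reported primary outcome; the baseline ratings are also not required to precede the allocation draw

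*Protocol article*

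**What the plan says.** The box on strengths and limitations in the protocol article ends with: "Blinded outcome assessment and standardised randomisation procedures are implemented to minimise bias".

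The section on blinding and randomisation names one person who is masked to the full allocation: "The study researcher responsible for analysing the primary outcomes will remain blinded to group allocation by working with a concealed group variable". The statistical analysis section repeats this, saying that the analysis "will be conducted by a researcher blinded to group assignments". The blinding section adds a partial mask: staff show the video separately, so that the consulting physicians do not learn who has seen it. For the other factor it says that "the physician must be aware of group assignment to conduct the informed consent process using augmented communication where applicable".

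On allocation, the same section says: "Each patient will draw one envelope on inclusion, thereby determining their group assignment by chance". The aDOC section places randomisation at the baseline visit, about four days before surgery, with the assigned intervention on the same day.

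The primary objective is headed as a subjective measure. It consists of a 0–10 pain rating "documented in a patient diary, and the Pain and State of Health Inventory (PHI". Table 1 obtains the Harris Hip Score by physician examination and survey, and DN4 by examiner or survey. The table's legend defines the first baseline point as "T-4a, 4 days preoperative, before the intervention". The pain NRS row gives T-4 without the a or b suffix.

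**The concern.** Blinded outcome assessment and blinded data analysis protect against different things. The first keeps knowledge of the group out of the measurement. The second keeps it out of the analyst's choices once the measurements exist. A reader judging risk of bias will credit the trial with the first, whereas the methods describe only the second.

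This matters more here than in most trials. The interventions are meant to change what patients expect, and the primary outcome is what patients say they feel. Ratings given by someone who knows which package they received can move through response bias as well as through real pain relief.

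The second issue is the reference point. The abstract says the primary analysis compares changes in pain intensity, and the first key question concerns preoperative expectations. If a patient has already learned the group when giving baseline ratings, those ratings may carry part of the effect under study.

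**Working it through.** **1. The claim against the methods.**

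| Who | What the article says about masking |
|---|---|
| Data analyst | Masked to group by a hidden label |
| Consulting physicians | Masked to the video factor only |
| Physician delivering aDOC | Must know the aDOC assignment |
| Patient (rates diary NRS and PHI) | Draws the envelope; no blinding described |
| Examiner for Harris Hip Score and DN4 | No masking stated |

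The assessor of the primary outcome is the patient, and no row masks the patient. The blinding section accepts a possible experimenter effect and says that blinding the study researcher is meant to limit it. A hidden label applied at analysis cannot act on diary entries that were completed earlier.

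**2. Does any planned figure change?** No. The stated n=164 can be reproduced with the within-between interaction formula λ = f²·N·m/(1−ρ). The article gives neither the number of measurements m nor the correlation ρ; I assume m=2 and ρ=0.5. With f=0.15 and N=164, λ = 0.0225×164×2/0.5 = 14.76 on 3 and 160 degrees of freedom, and power is 0.905 (N=160 gives 0.897). Other pairs also give 164, for example m=7 with ρ=0. Blinding does not enter this calculation.

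**3. What response bias could do (illustration; the shifts are assumed).** Suppose there is no true effect, but knowledge of the group shifts reported pain by b SD between two groups of n each. Then z = b/√(2/n), and the two-sided 5% rejection rate is Φ(z−1.96) + Φ(−z−1.96). All 200 patients are taken as analysed on a single pain score.

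| b (SD) | Factor main effect, 100 v 100 | One arm v TAU, 50 v 50 |
|---|---|---|
| 0.1 | 0.109 | 0.079 |
| 0.2 | 0.293 | 0.170 |
| 0.3 | 0.564 | 0.323 |

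For example, b=0.2 and n=100 give z = 0.2/0.1414 = 1.414, and the rate is Φ(−0.546) + Φ(−3.374) = 0.293. Analyst blinding leaves every entry unchanged.

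**4. Baseline order.** Draw, baseline visit and intervention fall on one day. The definition of T-4a places it before the intervention and says nothing of the draw. Two sequences are therefore compatible with the text: T-4a, draw, intervention; or draw, T-4a, intervention. For the pain NRS, the missing suffix means Table 1 does not even place the baseline rating before the intervention.

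Under the second sequence, let knowing the group shift the baseline difference by b, let the difference at follow-up be τ, and let r be the within-group correlation of baseline and follow-up, with equal SDs:

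- change score: expected estimate τ − b;
- baseline-adjusted: expected estimate τ − r·b.

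The documents give neither b nor r. With assumed b = 0.1–0.2 SD and r = 0.5, the bias is 0.1–0.2 SD and 0.05–0.10 SD respectively, for whichever outcome is shifted. It is towards zero if the baseline shift runs in the direction of the intended effect. Response bias at follow-up could act the opposite way, and nothing makes the two cancel.

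**The case against.** The strongest reply is that this is one loose summary item in an otherwise open article. The blinding section says the physician knows the assignment and that an experimenter effect is built in, and the primary objective is labelled subjective. Patients cannot realistically be masked to a video or a conversation, and expectation is the intended mechanism. That stands. The fault lies in the claim, not in open delivery, and a reader who inferred that the article conceals the problem would go too far.

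Several other stronger readings are tempting and unsupported:

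- *That the analyst is the only person masked to anything.* Consulting physicians are also masked to the video factor.
- *That the physicians who deliver aDOC rate the Harris Hip Score or DN4.* The article does not say who the examiners are. It states no masking for them, and no more can be concluded.
- *That baseline ratings are taken after the draw.* The order is left open. A condensed article may leave visit sequence to the full protocol, and it does not say who opens the envelope or what the patient is told. The patient involvement section also mentions a partial-disclosure condition. This may limit what patients know of the hypotheses, but it is not described as blinding to group.
- *That a known share of the planned effect is lost.* The article gives f=0.15 and no effect in SD units, so no such share can be calculated.

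The reply does not remove the main point, because the strengths item asserts a property that the methods do not describe. The baseline point also survives in a secondary role. The article does fix the timing of T-4a, but ties it to the intervention rather than to the draw.

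**Conclusion.** The point holds as a mismatch between claim and method. For the primary outcome, the stated safeguard of blinded assessment does not exist as described: patients report their own pain, draw their own allocation, and have no blinding described. What the article supports is blinded data analysis plus masking of consulting physicians to the video.

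The open baseline order is a lesser, conditional point. If allocation is known before T-4a, a shift b biases a change score by b and a baseline-adjusted estimate by about r·b.

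No sample-size or error-rate figure in the plan changes. The rejection rates and bias ranges shown rest on assumed shifts and on an assumed r of 0.5. They show what analyst blinding leaves untouched and do not estimate the bias in this trial.

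**What to change.** - **Strengths box:** replace the item on blinded outcome assessment with *blinded data analysis; the primary outcome is self-reported by unblinded patients*, and list this as a limitation.
- **aDOC section and blinding section:** state that all T-4a measures, including the baseline pain NRS, are completed before the envelope is opened. Mark the NRS in Table 1 as T-4a accordingly.
- **Harris Hip Score and DN4:** claim blinded assessment only if the existing examiners are in fact not told the group. Otherwise make no claim.

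The cost is a few sentences and a fixed order of steps within a visit that already takes place. No extra patients or assessments are needed. The downside is that the stated risk of bias looks less favourable.

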## Introduction

### Background

 Osteoarthritis (OA) is a common condition, especially in the ageing population.^1^ The hip joint is often affected, resulting in severe pain and functional impairments. Total hip arthroplasty (THA) is one of the most frequently performed surgical procedures worldwide, particularly in industrialised countries, such as Germany, providing significant pain relief and improved mobility.^2 3^ THA provides significant short-term and long-term benefits to patients' quality of life, including pain relief, improved functionality and increased overall satisfaction.^4 5^ Despite these benefits, a relevant proportion of patients continues to experience persistent postoperative pain, which affects functional recovery and satisfaction with surgery.^6 7^ As OA incidence continues to rise, preventing postoperative pain, optimising perioperative care and improving pain management remain a major focus of orthopaedic research.^3^

### Optimising treatment expectations to improve acute postoperative pain and prevent chronic pain after surgery

The severity and chronicity of pain following orthopaedic surgery are closely linked to psychological factors, such as preoperative expectations and emotional states.^8 9^ Early efforts to incorporate interventions targeting these expectations in surgical settings have demonstrated positive effects on postoperative pain outcomes, particularly in non-orthopaedic surgeries.^8^,^13^ However, empirical evidence within orthopaedic procedures, including THA, remains limited.

A promising approach in this regard is to target patients’ treatment expectations. Positive expectations have been shown to enhance treatment outcomes and play a crucial role in generating placebo effects, while negative expectations can weaken these effects, contributing to the nocebo phenomena.^14^,^17^

For instance, research has demonstrated that the anticipation of pain can profoundly alter its perception. The expectation of pain can transform a non-painful sensation into a painful experience or, conversely, reduce or even eliminate pain entirely.^18^ In contrast, experimental studies suggest that positive expectations not only modulate pain perception but also influence neural processing, thereby enhancing responses to both placebo and active treatments.^19^ This highlights the significant role of expectations in shaping postoperative pain outcomes, particularly in orthopaedic procedures. Therefore, systematically understanding the mechanisms and effects of expectations may be crucial for improving the prevention of pain and pain treatment efficacy in clinical populations, including patients undergoing THA. By optimising expectations within a therapeutic context, we could potentially enhance recovery, reduce postoperative pain and disability, and prevent chronic pain in a safe and cost-effective manner.^20 21^

### Methods to optimise treatment expectation: observational learning and augmented communication

Treatment expectations are shaped through various mechanisms, including conditioning based on prior experiences.^22^,^24^ Moreover, research suggests that these expectations can be influenced by observing others who have experienced positive treatment outcomes.^1025^,^27^ An additional mechanism relates to communication. Patients often benefit significantly from direct interaction with others, especially healthcare providers. However, such opportunities, for example, augmented communication, are often limited in clinical settings.^28^ While most of the existing evidence on the impact of expectations stems from experimental studies with healthy volunteers, it is important to recognise that the desire for pain relief may differ significantly between healthy individuals and patients undergoing surgery.^24^ In a clinical study, Stuhlreyer *et al*^29^ demonstrated that augmented physician communication aimed at improving treatment expectations significantly reduced postoperative pain after total knee arthroplasty. Building on these findings, it is obvious to address both methods to optimise patients’ treatment expectation and to investigate whether (1.) prerecorded videos of patients who have successfully benefited from the treatment, (2.) physician communication reflecting warmth and competence and (3.) a combination of both can maximise patients’ positive treatment expectations and enhance treatment outcomes.

### Study aims and questions

The aim of this study is to improve postoperative outcomes, particularly pain and functional disability, within the clinical context of pain management in patients undergoing THA. We will investigate the effects of physician communication and social observational learning on the dynamic changes in patients' treatment expectations and, consequently, on postoperative pain perception and functional impairments in patients undergoing THA.

The following are the key questions in this study:

Can augmented practitioner communication and/or a digital social observation learning intervention effectively optimise preoperative treatment expectations and emotional states in patients undergoing THA?Can preoperative expectation management, especially the combination of both strategies, result in improved postoperative health outcomes, especially in terms of pain and functional capacity?Do the effects of enhanced communication and social observational learning on expectations and on postoperative subjective and objective outcome dynamics combine in an additive or in a synergistic manner?Does expectation management enhance pain-related self-efficacy expectations, reduce preoperative anxiety and stress levels and impact postoperative recovery on subjective and physiological levels, including inflammatory markers?

## Method and Design

### Setting

The study will be conducted at the University Medical Center Hamburg-Eppendorf (UKE), Germany, as part of the Collaborative Research Centre (CRC) SFB 289. In addition to its own study-specific outcomes, the trial also contributes to centrally coordinated assessments defined by the CRC. These centrally collected measures serve overarching research aims and are implemented uniformly across all participating sub-projects (for a preregistration, see: OSF Registries | SFB289 - Central Project NeuroImaging). These centrally coordinated assessments include neuroimaging to examine structural and functional brain connectivity prior to the experimental procedures, as well as the collection of salivary biomarkers such as cortisol awakening response and alpha-amylase activity. In addition, participants complete a standardised set of psychological questionnaires. These data will contribute to cross-project analyses aimed at identifying individual predictors of expectancy-related effects, particularly in relation to stress responsiveness, affective disposition and pain sensitivity.^30^ The study is expected to begin in July 2025, with patient recruitment due to conclude by July 2026. The final follow-up assessments will end in July 2027.

